**Figure 1 F1:**
[figure not shown]
Code Stroke protocol^*^. ^*^Pathways may differ from site to site, based on already established workflow practices and available resources. CTA, CT angiography; ECR, endovascular clot retrieval; ED, emergency department; MRA, magnetic resonance angiography.

### Interventions

#### Code Stroke protocol development and implementation (all PACS sites)

A Code Stroke protocol^35
36^ is a hospital-based protocol and multidisciplinary emergency response system designed to standardise initial clinical assessment and urgent imaging of children with suspected stroke, informed by evidence-based guidelines.^28
29^ Components along the process of care, which begins on arrival in the ED, include recognition of symptoms associated with stroke^37^ at the time of triage, which leads to activation of Code. This triggers rapid clinical assessment by ED physicians. Neurologists will confirm the presence of neurological signs and assess the severity of symptoms using the paediatric adaptation of the National Institutes of Stroke Severity Scale (pedNIHSS),^38^ and in the context of ischaemic stroke, to screen children for eligibility and contraindications to reperfusion therapies, which includes collection of bloodwork. The clinicians decide the need for and type of brain imaging (CT or MRI) to confirm stroke diagnosis. Imaging leads to decisions about reperfusion therapies for ischaemic stroke or neurosurgical intervention for HS. An example of a Code Stroke pathway is presented in figure 1.

The five tertiary paediatric hospitals without established institutional Code Stroke protocols at commencement of the study will develop and implement the protocols through establishment of multidisciplinary working groups including—but not limited to—paediatric ED physicians, neurologists, neurosurgeons, radiologists, stroke research nurses, anaesthetists, intensivists, haematologists and neuro-interventional radiologists. Current practice will be evaluated through engagement of these stakeholders, and site-specific analysis of barriers and enablers to improving stroke diagnosis will be identified, drawing on previous conceptual modelling using Value Focused Process Engineering to map the process of care in children with suspected stroke.^39^

The remaining four tertiary paediatric hospitals with pre-existing Code Stroke protocols at commencement of the study (RCH, MCH, QCH and SCH) will further refine their protocols. They will partner with state ambulance services and adult comprehensive stroke centres to investigate the accuracy and clinical utility of a paediatric stroke decision support tool and automated perfusion imaging to improve diagnostic certainty and to select children most likely to benefit from reperfusion therapies. These hospitals will also function as knowledge hubs to assist the five other hospitals with development of their Code Stroke protocols.

#### Brain Attack and Stroke in Children Screen clinical decision support tool (PACS substudy)

The purpose of the Brain Attack and Stroke in Children Screen (BASICS) paediatric stroke recognition tool aims to increase diagnostic certainty for triage nurses and emergency physicians, using readily available demographics, process of care factors and neurological symptoms. The tool to be developed will provide the user with a probability of stroke versus mimic diagnosis and the probability of ischaemic versus HS to guide decisions about the need for Code Stroke activation and selection of CT- or MRI-based imaging. In addition to determining the probability of stroke, BASICS will allow the user to input the pedNIHSS variables to produce a stroke severity score which is essential for decisions about the use of reperfusion therapies.^28^ Unpublished pilot work using two retrospective patient cohorts suggests the tool has an overall accuracy of 84% for correct differentiation of childhood AIS from mimics and 89% for HS from mimics. A paper-based version of the BASICS decision support tool will be piloted at three hospitals (RCH, MCH and QCH). On completion of the PACS study, development of an app-based version is planned and functionality will need to be tested in a further prospective dataset (figure 2).

**Figure 2 F2:**
[figure not shown]
BASICS decision support tool. BASICS, Brain Attack and Stroke in Children Screen paediatric stroke recognition tool; PEDNIHSS, Paediatric National Institutes of Health Stroke Scale; tPA, tissue plasminogen activator.

#### Automated perfusion-diffusion software (PACS substudy)

Perfusion imaging has been demonstrated to be useful in adults to identify patients who are more likely to benefit from reperfusion therapies (eg, thrombolysis beyond 4.5 hours and ECR beyond 6 hours) by quantifying salvageable brain.^17^ PACS will investigate utility of iSchemaView RapidAI automated perfusion-diffusion software to guide decision-making for selecting children for thrombolysis and ECR. We have previously assessed the feasibility and utility of automated perfusion-diffusion imaging in a small retrospective cohort of children^19^ (figure 3).

**Figure 3 F3:**
[figure not shown]
Automated perfusion diffusion software. Example of automated diffusion perfusion MRI in a child with right middle cerebral territory infarction secondary to an M1 segment middle cerebral artery vessel occlusion ADC (left) and perfusion (right) images at three 75 hours post symptom onset showing a 23 mL mismatch between the perfusion and diffusion volumes, representing salvageable brain. ADC, apparent diffusion coefficient; Tmax, time to maximum residue function.

Data are acquired with CT perfusion or MRI diffusion-weighted and perfusion imaging. Calculation of parameters related to tissue flow (perfusion) and tissue blood volume is derived and presented visually (figure 3). A central imaging repository for all PACS study de-identified, processed RAPID perfusion maps/data will be housed at the Melbourne Brain Centre at The Royal Melbourne Hospital. Utilisation of RapidAI perfusion software will not be used by all centres and will be at the discretion of the neuroradiologist and associate investigators at participating PACS study sites.

### Study procedure post-protocol implementation at participating sites

In children with suspected stroke, where symptoms are considered suspicious for stroke, the ED team will activate a Code Stroke, resulting in rapid assessment by the neurology team. During the hours 08:30—18:00 on weekdays, the triage nurse/or ED nurse caring for the patient will notify the site PACS study nurse research coordinator of eligible children. The PACS study coordinator will follow the participant during their ED stay and track their progress. For children presenting after hours and on weekends, eligible cases will be identified through (1) notifications to the study coordinators from the on-call neurology team, (2) daily review of the ED triage list to identify potentially eligible patients and (3) direct triage notifications through the electronic medical record.

In children with relevant symptoms where stroke is not suspected, the patient discharge list in the ED triage system will be reviewed daily for participants presenting outside normal working hours (or if the PACS coordinator is unavailable during hours). This will allow the identification of children who present outside recruitment hours and data will be collected retrospectively. In participants who present after hours or who are discharged from the ED without PACS study coordinator involvement, the family will be contacted by phone within 5 days of discharge to obtain consent to continue. Participants with suspected stroke who do not undergo imaging will be contacted by phone call 6 weeks from their ED presentation to ensure there has been no change in the discharge diagnosis.

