### Study participants, inclusion and exclusion criteria

During the pre-implementation phase, from 2015 to 2017, children aged 1 month to 18 years with radiologically confirmed stroke will be retrospectively identified from ICD10 principal diagnosis codes for stroke and then medical record review.

During the Code Stroke protocol development and post implementation phases from 2018 to 2026, children aged 1 month to less than 18 years of age with symptoms of less than 24 hours duration that are suspicious for stroke (also referred to as brain attacks)^34^ will be eligible for recruitment to the PACS study. Symptoms include altered consciousness; focal face arm or leg weakness; dysarthria; dysphagia; sensory disturbance; visual disturbance; limb incoordination/ataxia; visual/sensory neglect; pupillary abnormality; severe headache with associated focal neurology and seizure(s) with associated focal neurology^28^ (figure 1). Patients will be categorised into two final diagnostic groups: stroke or mimics, based on presence or absence of acute ischaemic or haemorrhagic infarction on brain imaging. Stroke will be further sub-categorised into AIS or haemorrhagic stroke (HS) as adjudicated by a paediatric radiologist. Children with acute neurological symptoms that are not relevant for stroke will be excluded from the study.

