### Protocol development and post implementation phases

During this phase, data will be collected for children presenting to the ED with brain attack symptoms relevant for stroke.

For secondary aim (4), in participants with confirmed stroke, the health economic impact will be determined using the Child Health Utility-9D (CHU-9D) as a paediatric generic preference-based measure of health-related quality of life, to allow calculation of quality-adjusted life years (QALYs) in cost-utility analyses.^42^ Data will be entered into a REDCap database (table 1).

For secondary aim (5), the Paediatric Stroke Outcome Measures^40^ and the paediatric version of the modified Rankin Scale^41^ will be derived where possible if data are available for the retrospective patient cohort in the pre-implementation phase, and prospectively collected in the protocol development and post implementation phases.

The full list of data variables collected is detailed in online supplemental e-Table 2.

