## Data analysis plan

### Outcomes

The *primary outcome* is the change in the proportion of children with stroke diagnosed within a 4.5-hour time window for reperfusion therapies, pre- and post-PACS implementation. This will be estimated using a mixed-effect logistic regression model with the dichotomous variable ‘diagnosed within 4.5-hour time window (yes/no)’ as the dependent variable, implementation phase as an independent fixed effect and hospitals as random effects.

*Secondary outcomes* (figure 4) include:

The proportion of children receiving reperfusion therapies will be analysed as for the primary outcome.Accuracy of emergency medical services (EMS) call taker, paramedic and ED physician stroke diagnosis against the gold standard diagnosis of radiologically confirmed stroke. Change in correctness of stroke (vs mimic) diagnosis, pre-implementation and post implementation of PACS will be estimated using a random-effect logistic regression model with dichotomised correctness of diagnosis as the dependent variable, intervention phase as an independent variable and hospital as a random effect.The impact of EMS call taker, paramedic and ED physician actions (eg, lights/sirens response and prenotification, PACS activation, MRI selection as the first imaging study in suspected AIS) on time to diagnosis will be analysed. Differences in times will be analysed using clustered quartile regression, with hospitals as clusters.The economic impact of shorter time to diagnosis, increased utilisation of MRI imaging and increased rates of reperfusion therapy in stroke patients will be measured using the CHU-9D, and hospitals linked services health utilisation and cost data.

Markov cohort model will be developed to quantify per-capita, national healthcare and societal costs economic costs, and the associated lifetime loss of QALYs and life years.

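### Weekday daytime arrivals with the coordinator on duty have no stated list search for unsuspected stroke, so late and missed diagnoses may be under-captured in the post-implementation phase only

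*Protocol article*

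**What the plan says.** The section on study procedure after protocol implementation treats two groups separately.

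- **Stroke suspected.** On weekdays between 08:30 and 18:00, "the triage nurse/or ED nurse caring for the patient will notify the site PACS study nurse research coordinator of eligible children". After hours and at weekends there are three routes: notification by on-call neurology, daily review of the ED triage list, and triage alerts from the electronic record.
- **Stroke not suspected although symptoms are relevant.** The one stated search is that "the patient discharge list in the ED triage system will be reviewed daily for participants presenting outside normal working hours". The sentence does not stop there; with its exception, the review is "for participants presenting outside normal working hours (or if the PACS coordinator is unavailable during hours". Its stated purpose is to find children who come outside recruitment hours.

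Eligibility after 2017 is by symptoms: children "with symptoms of less than 24 hours duration that are suspicious for stroke". The data-collection section adds that "data will be collected for children presenting to the ED with brain attack symptoms relevant for stroke". The pre-implementation cohort (2015–2017) is identified from ICD-10 principal diagnosis codes followed by record review.

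Two outcomes depend on complete capture. The primary outcome is the change in the proportion of children with stroke diagnosed within 4.5 hours. A secondary outcome is "Accuracy of emergency medical services (EMS) call taker, paramedic and ED physician stroke diagnosis against the gold standard diagnosis of radiologically confirmed stroke".

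**The concern.** A stroke that nobody suspects in the ED is the case most likely to be diagnosed after 4.5 hours, and by definition it is a miss for ED recognition. A study of timeliness and recognition needs a search for these cases that does not depend on recognition. The plan has such a search for every time band except weekday daytime with the coordinator on duty. In that band the child enters if a nurse regards the child as eligible, and a nurse who does not suspect stroke has less reason to call.

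If such children are lost, they are lost from the post-implementation phase only, because the 2015–2017 code search takes no account of suspicion or arrival time. Late diagnoses would leave the post-phase denominator and false negatives would leave the sensitivity denominator. Both shifts favour the study hypothesis.

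**Working it through.** **Capture routes stated in the article**

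| Arrival | Stroke suspected | Stroke not suspected |
|---|---|---|
| Weekday 08:30–18:00, coordinator available | Nurse notification | No list search stated; nurse notification if the nurse judges the child eligible |
| Weekday 08:30–18:00, coordinator unavailable | Nurse notification | Daily ED discharge-list review |
| All other times | Neurology call, daily triage-list review, electronic alert | Daily ED discharge-list review |
| Pre-implementation, any time | ICD-10 codes and record review | ICD-10 codes and record review |

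**Is there a later backstop?** The six-week call is for suspected stroke without imaging, so it does not reach these children. A child who goes home and returns later may be past the 24-hour symptom limit. No ICD-10 check is stated for the post phase.

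**Size.** The plan gives no figure for unsuspected strokes or for arrivals by time of day, so there is no figure of its own to reproduce on this point. The inputs are:

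- *p*, the true proportion diagnosed within 4.5 hours: 40% post and 15% pre (sample size section).
- *s*, the share of strokes arriving in hours. The window is 9.5 h × 5 = 47.5 h of 168 h, or 28.3% of the week. Arrivals need not follow the clock, so 45% is assumed as an upper value.
- *q*, the share of strokes not suspected in the ED: assumed 10% to 30%.
- *c*, the share of in-hours unsuspected strokes that nurses still report: 0 in the worst case. The coordinator is taken as always on duty in hours.

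Share of strokes lost: L = s × q × (1 − c). If every lost case was diagnosed after 4.5 hours, the observed proportion is p / (1 − L). If an unsuspected stroke is equated with a missed ED physician diagnosis, the observed sensitivity is (1 − q) / (1 − L).

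Worst case, c = 0:

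| s | q | L | True 40% reads | True 15% reads | ED sensitivity, true → observed |
|---|---|---|---|---|---|
| 28.3% | 10% | 2.8% | 41.2% | 15.4% | 90% → 92.6% |
| 28.3% | 30% | 8.5% | 43.7% | 16.4% | 70% → 76.5% |
| 45% | 10% | 4.5% | 41.9% | 15.7% | 90% → 94.2% |
| 45% | 30% | 13.5% | 46.2% | 17.3% | 70% → 80.9% |

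For example, in the last row 0.30 × 0.45 = 0.135, 0.40 / 0.865 = 46.2% and 0.70 / 0.865 = 80.9%. Of 98 true post-phase strokes, about 3 (98 × 0.028) to 13 (98 × 0.135) would be lost.

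If nurses report half of these children (c = 0.5), L falls to 1.4% to 6.75%. A true 40% then reads 40.6% (0.40 / 0.986) to 42.9% (0.40 / 0.9325). With q = 30%, a true sensitivity of 70% reads 73.1% (0.70 / 0.958) to 75.1% (0.70 / 0.9325).

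**The case against.** A reader might infer that unsuspected strokes are searched for only outside working hours, that daytime misses have no way into the study, and that the results are therefore overstated. The documents support none of the three. The discharge-list sentence goes on to include daytime arrivals when the coordinator is unavailable. Nurse notification is a real route: eligibility rests on symptoms, not on activation of a Code Stroke or on a physician's suspicion. A child whom a nurse reports but the physician misses is captured and counts as a false negative. Nor must an unsuspected stroke be late: the clock runs from last seen well to completion of imaging, and a child imaged promptly for another reason can fall within 4.5 hours.

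Three further points have some force. The pre-phase search uses principal diagnosis codes, so it has gaps of its own and is not a perfect comparator. The Discussion already lists bias from mixing retrospective and prospective collection. Screening logistics are also detail that an article may leave to the full protocol.

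What remains is that the article does more than leave out a detail: it states a list search and limits it by time band. The general limitation neither names nor repairs this gap. Nurse notification relies on recognition by ED staff, which the article's Introduction itself treats as a weak link.

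**Conclusion.** The gap is real but narrow. It concerns weekday 08:30–18:00 arrivals, with the coordinator on duty, in whom stroke is not suspected. These children may be under-captured in the post phase. The likely direction is upward for both the proportion diagnosed within 4.5 hours and ED physician sensitivity.

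The size is not known. Under total loss with all lost cases late, and with the assumed 10–30% unsuspected and 28–45% arriving in hours, the primary proportion rises by 1.2 to 6.2 points at a true 40%. If the true post-phase proportion were still 15%, the rise would be 0.4 to 2.3 points. Against a planned change of 25 points this is modest and would not by itself create the effect sought. The sensitivity estimate is more exposed: up to about 11 points in the same worst case (70% read as 80.9%). Any capture by nurses shrinks all of these figures. The point is worth correcting because the error would favour the hypothesis and the remedy is cheap, but it does not invalidate the design.

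**What to change.** Remove the time-band restriction. State that the ED triage and discharge lists are reviewed daily for all presentations, at all sites, against the same symptom list, whether or not the coordinator was on duty and whether or not stroke was suspected.

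Sites were approved between August 2021 and September 2023 and collection runs to mid-2026, so a change made only from now on would alter ascertainment within the post phase. For arrivals already past, either search the stored daytime lists in the same way or apply to the post phase the ICD-10 search already specified for 2015–2017. Report the cases recovered this way separately, so that readers can see how many were missed and how far the two outcomes move.

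The cost is modest extra coordinator time, since the lists are already part of daily work, plus the retrospective search. Some recovered cases will have data collected retrospectively, as the plan already accepts for after-hours arrivals.

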## Data collection

### Pre-implementation and pre-protocol development phase

All sites will retrospectively collect data for confirmed strokes by case record review from 2015 to 2017, using the ICD-10 codes: I61.0–I61.6, I61.8, I61.9, I62.9, I63.0–I63.6, I63.8, I63.9, I64.0 and G45, for the primary aim of determining time to diagnosis prior to implementation of Code Stroke protocols across study sites (table 1).^40
41^

**Table 1 T1:** Data to be collected

Variables	Pre-implementation (2015–2017) confirmed stroke	Post implementation phase (2018 onwards) stroke	Post implementation phase (2018 onwards) mimics
Demographics	✓	✓	✓
Prehospital care*	✓	✓	✓
Presenting clinical features	✓	✓	✓
pedNIHSS (baseline, 24 and 48 hours)	✓†	✓	✓‡
EMS call taker and paramedic coded diagnoses*	✓	✓	✓
Sensitivity of ED physician diagnosis		✓	✓
Time to diagnosis§	✓	✓	✓
Timelines of care (pre- and post-arrival)	✓	✓	✓
Length of stay, acute hospital and inpatient rehabilitation	✓	✓	✓¶
Follow-up phone call following ED discharge for mimics to confirm no change in diagnosis		✓	✓
Rates of reperfusion therapy use (t-PA and ECR)	✓	✓	
Reperfusion therapy related serious adverse events	✓	✓	
Neurological outcomes: Outcomes: (PSOM and mRS) at discharge 7, 30 and 90 days. mRS at 30 and 90 days	✓	✓	
Child Health Utility (CHU-9D)		✓	
Costs of childhood stroke, using hospital/Medicare linked services health utilisation cost data		✓	

* For the subgroups of children transported to ED by ambulance.

† Paediatric version National Institutes of Health Stroke Scale (pedNIHSS) and Paediatric Stroke Outcome Measures (PSOM) may be derived retrospectively in some (but not all) patients from clinical assessment notes and should be collected if applicable.

‡ Only at baseline.

§ Time to diagnosis will be collected for all children presenting to the emergency department, regardless of mode of arrival and for inpatients where a Code Stroke is activated.

¶ Only if admitted.

ECR, endovascular clot retrieval; ED, emergency department; EMS, emergency medical services; mRS, modified Rankin score; tPA, tissue plasminogen activator.

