## Sample size and power calculations

We anticipate 326 patients with suspected stroke will be recruited during the protocol development and prospective phases of the study (based on numbers of patients recruited to institutional stroke registries in Victoria and New South Wales). Recent literature suggests that approximately one in three children with stroke symptoms will have a final diagnosis of stroke following imaging.^31
43–45^ Therefore, we anticipate 98 participants with a radiologically confirmed diagnosis of stroke in each study phase. Estimates of pre-implementation time to stroke diagnosis are based on extrapolation of local published data^13^ and audit data provided by three study sites. Estimates of post implementation time to stroke diagnosis are based on audit data from Queensland Children’s Hospital, where the proportion of children diagnosed within 4.5 hours increased from 15% to 40% during the 12-month period following introduction of their institutional PACS in 2019. We estimate that 15% of children will be diagnosed within 4.5 hours in the pre-implementation phase, increasing to 40% in the post implementation phase.

The *primary outcome* is the change in the proportion of children with stroke diagnosed within a 4.5-hour time window for reperfusion therapies, pre- and post-PACS implementation (figure 4). Time to diagnosis will be based on radiological confirmation of ischaemic infarction or haemorrhage on CT or MRI. This will be determined by calculating the time elapsed from last seen well to completion of neuroimaging, which is electronically recorded on imaging studies.

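### The closed ICD-10 search for 2015–2017 cannot find subarachnoid, subdural or extradural bleeds, while the post phase counts haemorrhage with no limit by type

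*Protocol article*

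**What the plan says.** **Pre phase.** Under Study participants, inclusion and exclusion criteria, children with radiologically confirmed stroke in 2015–2017 are "retrospectively identified from ICD10 principal diagnosis codes for stroke and then medical record review". The section Pre-implementation and pre-protocol development phase gives the codes: "I61.0–I61.6, I61.8, I61.9, I62.9, I63.0–I63.6, I63.8, I63.9, I64.0 and G45". It says the data are collected "for the primary aim of determining time to diagnosis prior to implementation of Code Stroke protocols across study sites", so this search supplies the baseline of the primary comparison.

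**Post phase.** From 2018, children are eligible with "symptoms of less than 24 hours duration that are suspicious for stroke". No diagnosis code is involved. They are then classed as "stroke or mimics, based on presence or absence of acute ischaemic or haemorrhagic infarction on brain imaging", and the next sentence reads "Stroke will be further sub-categorised into AIS or haemorrhagic stroke (HS) as adjudicated by a paediatric radiologist".

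**Outcome.** Under Sample size and power calculations, time to diagnosis rests on "radiological confirmation of ischaemic infarction or haemorrhage on CT or MRI". The type of haemorrhage is not restricted, and the rule is not tied to one phase.

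**Model.** Under Data analysis plan, Outcomes, the mixed-effect logistic model has implementation phase as its fixed effect and hospitals as random effects. No term for stroke type is stated.

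**The concern.** The primary estimate is a before-and-after contrast, so both phases must find the same kinds of case. The pre-phase search is closed and itemised by subcode. Within I62 it takes only I62.9, and it takes nothing from I60. Under the standard labels of the classification, the missing codes are subarachnoid (I60), subdural (I62.0) and extradural (I62.1) haemorrhage. Record review cannot restore these children, because review starts from the coded list.

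The post phase has no such filter. Its entry symptoms include altered consciousness, pupillary abnormality and severe headache with focal signs, and the outcome rule accepts haemorrhage without qualification. A child with a subarachnoid bleed and qualifying symptoms would meet the outcome rule in either phase, but could be found only in the later one.

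If such children differ from other strokes in how often they are diagnosed within 4.5 hours, the post-phase proportion moves even if Code Stroke does nothing. With phase as the only fixed effect, that movement is read as an intervention effect. Adjusting for ischaemic versus haemorrhagic type would not remove it, because the mismatch lies within the haemorrhagic group.

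**Working it through.** **1. The two routes side by side**

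| Type | Pre-phase search | Post phase |
|---|---|---|
| Ischaemic stroke (I63) | found | found |
| Intracerebral haemorrhage (I61) | found | found |
| Unspecified intracranial haemorrhage (I62.9) | found | found if imaging shows haemorrhage |
| Subarachnoid (I60) | not searched | not excluded |
| Subdural, extradural (I62.0, I62.1) | not searched | not excluded |

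The first three rows are common to both phases. The last two are the mismatch.

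**2. The plan's own sample size.** Inputs from Sample size and power calculations: 15% versus 40%, alpha 0.05 (taken as two-sided), intraclass correlation 0.05, coefficient of variation 0.5, 14 children per hospital per phase, seven hospitals.
- Individual-level size for 80% power: 49 per phase.
- Design effect: 1 + ((0.5² + 1) × 14 − 1) × 0.05 = 1.825.
- 49 × 1.825 = 89.4, which is 6.4 hospitals of 14. Rounded up to seven hospitals, this is 98.
- At 98 per phase the effective size is 98 / 1.825 = 53.7. Power is 0.837 (pooled z), 0.775 (continuity-corrected) or 0.792 (t, 12 df).

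The stated 98 and 80% reproduce. The mismatch does not alter this formula; it bears on bias.

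**3. Possible shift with no true effect.** The documents give neither the share of unlisted bleeds nor their on-time rate, so both are assumed. Let s be their share of post-phase strokes and a their on-time proportion, with all other strokes at the plan's 15%.

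Post-phase proportion = (1 − s) × 0.15 + s × a, so the shift = s × (a − 0.15).

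| s | a | Post-phase proportion | Shift (points) |
|---|---|---|---|
| 5% | 40% | 0.1425 + 0.020 = 16.3% | +1.3 |
| 10% | 60% | 0.135 + 0.060 = 19.5% | +4.5 |
| 15% | 70% | 0.1275 + 0.105 = 23.3% | +8.3 |
| any | 15% | 15.0% | 0 |
| 20% | 0% | 0.120 + 0 = 12.0% | −3.0 |
| 30% | 80% | 0.105 + 0.240 = 34.5% | +19.5 |

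The first three rows are the illustrative range. The last two show how far more extreme assumptions reach in each direction.

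**4. What a shift does to the test.** At effective size 53.7 (pooled z), the chance of declaring an increase when Code Stroke has no effect rises from 0.025 to 0.037 for s = 5%, a = 40%, and to 0.089 for s = 10%, a = 60%.

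**The case against.** The strongest reply is that the outcome rule applies to both phases and pre-phase cases must also be radiologically confirmed, so there is one imaging-based definition and only the route to the cases differs. That is right, and it narrows the point to case finding. It does not remove it: a common definition cannot be met in the pre phase by a search that leaves out some of its cases.

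A second reply is that the article never says subarachnoid, subdural or extradural bleeds count as haemorrhagic stroke. It leaves the subtype to a paediatric radiologist, and the full protocol may define it more narrowly. Entry is also limited by symptoms, since headache qualifies only with focal neurology. These points stand as reasons the mismatch may be small. The asymmetry in the published text remains: a closed list on one side and no list on the other.

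Third, the direction is not documented. The Introduction says CT is poorly sensitive for infarction in arterial ischaemic stroke, which makes earlier confirmation of bleeds plausible, but nothing says the omitted bleeds are diagnosed sooner. This stands.

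The Discussion acknowledges bias from mixing retrospective and prospective collection. That caveat is general; it neither identifies nor corrects this gap.

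Three stronger readings are tempting but unsupported:
- A reader might infer that the phases count different diseases. They do not: ischaemic stroke and intracerebral haemorrhage are common to both.
- A reader might take "based on presence or absence of acute ischaemic or haemorrhagic infarction on brain imaging" to class every primary bleed as a mimic. The next sentence makes haemorrhagic stroke a subtype of stroke, so this is loose wording and not an exclusion.
- A reader might infer that G45 brings transient ischaemic attacks into the pre-phase denominator. Radiological confirmation is already required, so G45 cases without it drop out.

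**Conclusion.** The concern holds as a partial case-finding mismatch confined to the haemorrhagic group. Followed as written, the plan lets some types of bleed be counted only in the post phase, and the stated model passes any resulting difference into the phase effect.

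Size and direction cannot be fixed from the documents. Assuming a 5–15% share and a 40–70% on-time rate, the shift is about 1 to 8 points against the planned 25. It is zero at an on-time rate equal to that of other strokes and negative below it. A reader might conclude that the plan is biased in favour of Code Stroke; the documents support only that it could be. The sample size of 98 per phase is unaffected. The gap is worth closing before analysis because it sits in the primary comparison and the correction is small.

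**What to change.** 1. Name the same non-traumatic haemorrhage types as stroke in both phases.
2. Then do one of the following:
   - Add I60 and I62.0–I62.1 to the 2015–2017 search. The cost is one further coding query per site and a small number of extra records to review.
   - Restrict the primary analysis set in both phases to the haemorrhage types on the current list. The cost is one sentence and the loss of some post-phase cases: on the assumed 5–15% share, about 5 to 15 of 98 (98 × 0.05 = 4.9; 98 × 0.15 = 14.7).
3. Add an analysis restricted to arterial ischaemic stroke. This mismatch does not affect it, and the subtyping is already planned. Its cost is fewer cases and so less precision; the article does not give the split.
4. As a wording correction only, align the stroke/mimic rule under Study participants with the outcome rule under Sample size and power calculations, so that it reads infarction or haemorrhage.

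G45 needs no change. Data collection runs to mid-2026, so either option in step 2 is still feasible, and neither adds a study procedure.
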